**5.5.2.- Exclusion criteria:**

- Patients who do not sign the informed consent form.
- Emergency medical condition in which it is not possible to collect study data.
- Heart condition requiring the use of hypothermia or hyperthermia during CPB.
- Patients without a minimum time of 60 minutes before decannulation (after the end of myocardial reperfusion, unclamping of the aorta and the end of CPB).
- Patients who cannot manage their fluid balance on their own through diuresis prior to CPB.
- Patients who are unable to manage excess volume during the surgical procedure by means of spontaneous or forced diuresis with diuretics (positive cumulative balance despite intravenous bolus of diuretics after 75% of the anticipated duration of CPB according to the course of the surgery).

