**5.- Methodology**

**5.1.- Study design**

A randomized, patient- and data analyst-blinded clinical trial to compare outcomes in terms of the lactate clearance rates (quantity/unit of time) of the assigned therapy groups. Two treatment groups will be established: one control group without hemofiltration (CG or 1), one group with hemofiltration using a polysulfone filter (PG or 2).

To ensure an unbiased assessment of treatments, randomization will be performed in eight blocks of five patients. The study groups will be equivalent in all aspects except the procedures they undergo.

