**5.5.- Choice of sample**

**5.5.1.- Inclusion criteria:**

- Patients who sign the informed consent form.
- Patients not undergoing emergency surgery.
- Surgical procedures performed under normothermic conditions.
- Patients with a minimum time of 60 minutes before decannulation (after the end of myocardial reperfusion, unclamping of the aorta and the end of CPB).

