**5.8.- Limitations of the study and ethical considerations**

The study design does not allow the use of total blinding, and the perfusionist is aware of the therapy and characteristics of the membrane at all times. According to the literature and standard practice in this country, the use of a control group should not pose any ethical dilemma if certain premises are taken into account.

The only condition that the control group must meet is that the patients must be able to manage their fluid balance by themselves, as a fluid overload has been shown to be harmful. This may mean that the patients in the control group have better renal function than those in the other group, or at least better initial diuresis. However, the primary objective is not to measure or evaluate perioperative renal function. In addition, a hemofilter will be available for use if control patients are not able to manage their fluid balance through diuresis. Finally, if surgery times are shorter in the control group, the lactatemia levels may be lower than in the other group with a longer duration. If this is the case, we will stratify the treatment groups by selecting cases with a shorter duration. In any case, a minimum time of 60 minutes is established from start of CPB + CUF and to the end of CPB.

It will be carried out according to the international ethical recommendations (the Declaration of Helsinki and the Oviedo Convention), since the use of the best available therapy according to the patients' circumstances is contemplated at all times.

In order to safeguard confidentiality, all personal data collected as part of this study will be treated in accordance with Organic Law 15/1999, of December 13, on personal data protection.

Likewise, informed consent will be requested for surgery that includes the usual CPB procedures with or without hemofiltration.

Informed consent will also be requested for use of any data deriving from medical records and analytical determinations. Access to personal information will be restricted to the investigator and authorized personnel and all of them will be obliged to maintain confidentiality. If the work is published, the patients' identity will remain anonymous at all times.

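### A fluid-balance exclusion judged late in bypass acts after allocation and falls mainly on controls, and the protocol does not say how controls who fail are analysed

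*Protocol*

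**What the plan says.** - **The late criterion.** The last item in Protocol 5.5.2 excludes "Patients who are unable to manage excess volume during the surgical procedure by means of spontaneous or forced diuresis with diuretics". It is defined as a "positive cumulative balance despite intravenous bolus of diuretics after 75% of the anticipated duration of CPB".
- **An earlier criterion.** The item before it excludes "Patients who cannot manage their fluid balance on their own through diuresis prior to CPB". This one can be applied before allocation and to everyone.
- **Control group.** Protocol 5.8 presents self-managed fluid balance as the one condition that controls have to satisfy. It accepts the consequence: "This may mean that the patients in the control group have better renal function than those in the other group", or at least better diuresis at the outset. It sets this aside because renal function is not the primary objective.
- **Controls who fail.** The same section adds that "a hemofilter will be available for use if control patients are not able to manage their fluid balance through diuresis".
- **Equivalence.** Protocol 5.1 states: "The study groups will be equivalent in all aspects except the procedures they undergo".
- **The 60-minute minimum.** Protocol 5.5.1 requires "Patients with a minimum time of 60 minutes before decannulation", with a bracket that refers to reperfusion, unclamping and the end of bypass; 5.5.2 mirrors it. Protocol 5.8 instead says that "a minimum time of 60 minutes is established from start of CPB + CUF and to the end of CPB".

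**The concern.** An exclusion is harmless to a randomised comparison when it is settled before allocation, or when it cannot depend on the arm. The late fluid-balance criterion meets neither condition. It is read during treatment, and the treatment itself changes the quantity being read.

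The selection variable is also tied to the outcome. Protocol section 3 names renal failure among the situations in which hyperlactatemia cannot be controlled during bypass. If patients who cannot clear fluid tend to have higher lactate, taking them out of one arm lowers that arm's mean without any treatment effect. The hypothesis of lower morbidity and mortality in 4.2 is exposed in the same way.

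The decision is open to influence as well. By 5.8 the perfusionist knows the therapy throughout. Lactate is measured every 20 minutes, so serial values exist before the judgement is made. The threshold uses an expected duration that may be revised as surgery proceeds.

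**Working it through.** **The plan's own figure.** There is no power calculation to reproduce. Section 5.6 gives about 40 patients as a feasibility estimate; eight blocks of five in 5.1 give 8 × 5 = 40, which agrees. Arm sizes are not stated; 20 per arm is assumed below.

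**Step 1: timing.** The criterion is read after 75% of expected bypass time. Section 5.8 counts its minimum from the joint start of bypass and ultrafiltration, so the filter starts with bypass. The protocol does not state when randomisation occurs, but the arm must be known before a filter can be started or withheld. The criterion therefore acts after allocation and after treatment has begun.

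**Step 2: which arm.** Section 3 describes the filter as removing fluid, with replacement, toward a net balance of zero. A positive balance that persists despite diuretics is then mainly a control-arm event. Section 5.8 points the same way by attaching the condition to controls.

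**Step 3: controls who fail.** Section 5.5.2 excludes such a patient; 5.8 makes a hemofilter available to the same patient. Neither section, nor 5.7, says whether that patient is analysed or in which arm.

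**Step 4: size of the shift in the control mean.** Assume that fluid-handling failure is a standard normal liability with correlation r to lactate, and that the worst share p of controls is removed. The retained mean shifts by −r × φ(z) / (1 − p), where z is the (1 − p) normal quantile.

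| p | z | φ(z) | φ(z)/(1 − p) | r = 0.2 | r = 0.5 |
|---|---|---|---|---|---|
| 10% | 1.282 | 0.1755 | 0.195 | −0.039 SD | −0.098 SD |
| 30% | 0.524 | 0.3477 | 0.497 | −0.099 SD | −0.248 SD |

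Simulation gave −0.038 and −0.250 SD at the two extremes. With 20 controls, 10–30% is 2–6 patients.

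**Step 5: effect on the test.** Here a share f of patients in each arm handles fluid poorly and has lactate d SD higher, and these patients are removed from control only. The bias is f × d. A two-sided 5% t-test with 20 per arm was simulated 20,000 times per scenario.

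| f | d | Bias against hemofiltration | False finding of harm, no true effect | Power for an assumed 0.9 SD reduction: all kept → controls removed |
|---|---|---|---|---|
| 5% | 0.5 | 0.025 SD | 3.2% | 78.6% → 76.1% |
| 20% | 1.0 | 0.20 SD | 7.7% | 73.7% → 49.2% |
| 30% | 1.0 | 0.30 SD | 11.4% | 71.6% → 34.8% |

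The nominal rate for a false finding of harm is 2.5%. If d = 0 there is no bias, only lost precision. The difference detectable with 80% power is (1.960 + 0.842) × √(1/n + 1/20), where n is the number of controls. It rises from 0.886 SD with 20 controls to 0.940 SD with 16.

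**Step 6: cost of keeping filtered controls.** The powers with all patients kept in step 5 assume no filter use in controls. If a share c of controls receives the filter and gains the full assumed 0.9 SD (an upper bound), the contrast shrinks by 0.9c, which is 0.09 SD at 10% and 0.27 SD at 30%. At 20% it is 0.9 − 0.18 = 0.72 SD, close to the 0.9 − 0.20 = 0.70 SD left by removing those controls when d = 1.0.

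**The case against.** The strongest reply is that several tempting conclusions go beyond the text.

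- **Only controls are removed.** A reader might infer this, but 5.5.2 is worded for both arms, and section 3 lets the balance in filtered patients vary with anaesthetic fluids. Also, the remark in 5.8 about better diuresis at the outset fits the pre-bypass criterion at least as well as the late one. What stands is that the late criterion falls mainly on controls.
- **Controls who receive the filter are dropped.** Section 5.8 says only that a filter is available. A control filtered before the 75% point might never show the defining positive balance. What stands is that their handling is unstated.
- **The sickest controls go, and fewer than 40 are analysed.** Poor late fluid balance may reflect fluids given, and patients unable to manage balance before bypass are already excluded. The figure of about 40 is a recruitment estimate, and replacement is not addressed. Neither inference is supported.
- **The bias is small and runs against the trial's hypothesis.** At 20 per arm the standard error of the difference is √(2/20) = 0.32 SD, larger than the whole 0.04–0.25 SD range. This is fair as to size, but a bias is not averaged away as random error is.
- **The fix may gain no power.** Step 6 shows that this can be so. But dilution only shrinks a real effect; selective removal can produce a difference where there is none.

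Section 5.8 discloses the imbalance, and 5.7 plans regression if the groups differ. Neither brings excluded patients back. Nor can this be left to an unseen analysis plan, because the exclusion is fixed in the protocol.

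**Conclusion.** The protocol is wrong as written on this point. An exclusion read late in bypass acts after allocation and mainly on controls. Together with the control-group condition in 5.8, it contradicts the equivalence claimed in 5.1. The timing and the concentration in controls are inferences from the protocol's description of the technique, and strong ones.

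The direction is probably against hemofiltration, provided that poor fluid handling goes with higher lactate, as section 3 suggests for renal failure. The size cannot be known from the document: about 0.04–0.25 SD on the assumed 10–30% removed and correlation of 0.2–0.5, and no bias if fluid handling is unrelated to lactate.

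The 60-minute minimum shares the timing problem and is defined in two ways. A reader might take it as further evidence of one-sided removal, but nothing in the document shows that it acts differently by arm.

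**What to change.** 1. Do not use the intraoperative fluid-balance criterion to remove randomised patients from the analysis. Base eligibility on what is known before allocation and apply it equally to both arms; the pre-bypass diuresis criterion in 5.5.2 already exists for this.
2. State that the primary analysis includes every randomised patient in the assigned arm. Keep controls who receive the filter in the control group, record that use, and report their exclusion only as a sensitivity analysis.
3. Reconcile 5.5.2 and 5.8 on controls who fail fluid balance, and align the equivalence statement in 5.1 with the result.
4. Reconcile the two definitions of the 60-minute minimum (5.5.1 and 5.5.2 against 5.8), and do not use it to drop patients after randomisation.

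When a control patient receives the filter remains the investigators' decision; these changes concern only who is analysed and how. The cost is amendment wording and some dilution of the contrast, at most 0.09–0.27 SD if 10–30% of controls cross over and gain the full assumed 0.9 SD.

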**5.6.- Sample size**

The sample size will result from the prospective inclusion of a consecutive series of patients over 10 months who undergo surgery with CPB by the investigator in the Cardiovascular Surgery Unit of Puerta del Mar University Hospital, Cádiz, under normothermic conditions. As a preliminary analysis, this cohort is estimated to consist of about 40 patients in the Cardiovascular Surgery Unit.

The study population will comprise a sample of patients who meet the inclusion criteria between February 2017 and December 2017.

**5.7.- Statistical analysis [24]:**

- Descriptive analysis of variables: measures of central tendency and dispersion will be shown in the case of quantitative variables, while frequencies and proportions will be shown in the case of categorical variables.
- The normality of the variables will be checked using graphs and the Kolmogorov-Smirnov test.
- Homogeneity and comparability between the groups of the two arms of the study in the main confounding factors considered will be verified at the beginning of the study by means of a comparison of proportions (chi-squared test or Fisher's exact test, if necessary) and a comparison of means (Student's t-test and the Mann-Whitney U test in case of non-parametric distributions).
- The intrasubject change over time will be analyzed by comparing paired means using a t-test or Wilcoxon signed rank test (non-parametric variables), quantifying the change in each measure in relation to the baseline reference measure (first sample).
- The bivariate analysis between the CG and PG will be performed using the chi-squared test or Fisher's exact test, if necessary, and using a comparison of means (Student's t-test and Mann-Whitney U test in case of non-parametric distributions).
- In the event of non-homogeneity in any variable between the groups studied, a multivariate analysis will be performed using linear regression.

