**4.2.- Hypothesis:**

- Continuous ultrafiltration with volume replacement using a polysulfone membrane during CPB in patients undergoing cardiac surgery decreases intraoperative lactatemia.
- Patients undergoing cardiac surgery and continuous ultrafiltration with volume replacement using a polysulfone membrane have a lower postoperative morbidity and mortality rate than patients undergoing cardiac surgery without hemofiltration.
- Patients undergoing cardiac surgery and continuous ultrafiltration with volume replacement using a polysulfone membrane have a better health status after surgery than patients undergoing cardiac surgery without hemofiltration. (Assessed by NNN taxonomies: NANDA, NOC, NIC).

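### Section 5.7 ties lactate change only to paired within-patient tests and does not say that the between-arm comparison applies to it

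*Protocol*

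**What the plan says.** Hypothesis 1 (protocol, section 4.2) is that continuous ultrafiltration with volume replacement "using a polysulfone membrane during CPB in patients undergoing cardiac surgery decreases intraoperative lactatemia". Section 5.1 describes a randomised two-group trial meant "to compare outcomes in terms of the lactate clearance rates (quantity/unit of time) of the assigned therapy groups". Both pose a question about the difference between arms.

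Section 5.4 lists serum lactate as the first dependent variable. It is sampled at the start of CPB, at 10 minutes, every 20 minutes, and 20 minutes after CPB ends. A preoperative serum lactate is also listed.

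Section 5.7 then gives three relevant items:

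- **Change over time:** "The intrasubject change over time will be analyzed by comparing paired means using a t-test or Wilcoxon signed rank test", with each measure referred to the first sample as baseline. The item covers any repeated measure, lactate included.
- **Between arms:** "The bivariate analysis between the CG and PG will be performed using the chi-squared test or Fisher's exact test" for categorical variables, and a t-test or Mann-Whitney test for quantitative ones. No outcome or time point is named.
- **Adjustment:** "In the event of non-homogeneity in any variable between the groups studied, a multivariate analysis will be performed using linear regression".

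**The concern.** Change from the first sample is attached to one method only, and that method does not compare the arms. Pooled over all patients, a paired test describes what lactate does during surgery and says nothing about filtration. Run separately by arm, it gives two p-values that are easily read as a contrast: lactate changed in one arm and not in the other. That pattern is not evidence of a difference between arms, because a significant and a non-significant result can come from identical true changes.

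The design makes this reading more likely. Section 5.8 expects lactate to depend on the length of surgery whatever the treatment. The sampling schedule also yields several paired tests per arm, each with its own chance of being significant in one arm only. The first hypothesis of the trial could be declared supported on such a pattern.

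**Working it through.** **Inputs**

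- Total: about 40 (section 5.6), which agrees with eight blocks of five (section 5.1): 8 × 5 = 40. This is a recruitment estimate. No effect size, SD, significance level or power is given, so there is no sample-size calculation to reproduce.
- Per arm: the allocation ratio is not stated. I assume 20. If every block of five split 2:3 the same way, the arms would be 8 × 2 = 16 and 8 × 3 = 24.
- Significance level: not stated. I assume two-sided 5%.
- True mean change *d*, in SDs of the change: not stated. I vary it from 0 to 1.0 and keep it **the same in both arms**, so filtration has no effect on change.

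**Step 1: power of the paired test in one arm.** *p* is the probability that a noncentral *t* variable, with *n* − 1 degrees of freedom and noncentrality *d*√*n*, exceeds the two-sided 5% critical value in size. Example: *d* = 0.46, *n* = 20, noncentrality 0.46 × √20 = 2.06, *p* = 0.497.

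**Step 2: discordant results.** The arms are independent, so P(exactly one arm significant) = 2*p*(1 − *p*), and P(filter arm only) = *p*(1 − *p*). Example: 2 × 0.497 × 0.503 = 0.500. The table uses unrounded *p*.

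| Common change (SD) | *p*, 20 per arm | Exactly one arm significant | Filter arm only |
|---|---|---|---|
| 0 | 0.050 | 9.5% | 4.8% |
| 0.2 | 0.136 | 23.5% | 11.7% |
| 0.3 | 0.247 | 37.2% | 18.6% |
| 0.4 | 0.397 | 47.9% | 23.9% |
| 0.46 | 0.497 | 50.0% | 25.0% |
| 0.5 | 0.565 | 49.2% | 24.6% |
| 0.6 | 0.721 | 40.2% | 20.1% |
| 0.8 | 0.924 | 14.1% | 7.0% |
| 1.0 | 0.989 | 2.3% | 1.1% |

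With equal arms, the control-only pattern is as likely as the filter-only one. If the common change is a fall, filter-only flatters filtration; if it is a rise, control-only does.

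**Step 3: unequal arms.** At 0.46 SD, *p* is 0.406 with 16 patients and 0.579 with 24. P(exactly one) = 0.406 × 0.421 + 0.579 × 0.594 = 0.171 + 0.344 = 51.5%. So the 25% ceiling for one named arm belongs to equal arms. Under this extreme split it would be 17.1% or 34.4%, depending on which arm is larger.

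**Step 4: the between-arm test.** In 100,000 simulated trials of 20 per arm at each of 0, 0.3, 0.46, 0.6, 0.8 and 1.0 SD, a two-sample *t*-test on the change was falsely significant in 4.95% to 5.11%. The same simulations gave discordant paired tests in 50.0% at 0.46 SD and 2.2% at 1.0 SD, in line with the formula.

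These rates are for one time point.

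**The case against.** The strongest reply is that a between-arm test is already planned. The item directly after the paired tests compares the control and filter groups by means, lactate heads the list of dependent variables, and section 5.1 names clearance rate, itself a measure of change, as the thing compared between groups. In a randomised trial, comparing intraoperative lactate levels between arms would answer hypothesis 1 without any change score. The variable and time point may be named in an SAP that is not shown.

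Most of this stands. A reader might infer that the protocol contains no test able to show an effect on lactate, and that would be wrong. It is also true that nothing in the protocol says the paired tests will be run by arm or used to judge hypothesis 1. They fit the descriptive aims in section 4.4.

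What the reply does not remove is the mismatch inside section 5.7. The protocol does not merely leave the analysis of change open: it assigns change to a method without an arm term, while its hypothesis and design statement ask about arms. The two-sample item is not linked to change, clearance or any time point, and the regression is conditional on imbalance.

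Two further inferences should be resisted. One is that lactate moves in every patient on bypass. Section 3 reports intraoperative hyperlactatemia in 10% to 21%, and section 5.8 only links lactate to duration. The other is that discordance would occur about half the time. That is the worst case.

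**Conclusion.** The point holds in a limited form. Section 5.7 attaches change from baseline only to paired within-patient tests, which cannot show a treatment effect. It does not say that the planned between-arm comparison applies to lactate change or clearance, and it lists no analysis that links arm with time.

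The size is conditional. If the paired tests were read side by side with no true difference, exactly one arm would be significant in about 2% to 50% of trials for a common change of 0 to 1.0 SD, against 5% for a two-sample test on change. With equal arms, at most 25% would be significant in the filter arm only. This assumes 20 per arm, two-sided 5%, normally distributed changes and a single time point. The protocol gives no SD or expected change, so the trial cannot be placed on that range. The remedy is worth making because it is cheap and closes off an invalid route to the main claim.

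**What to change.** In section 5.7, state that hypothesis 1 is judged only by the between-arm difference in intraoperative lactate, reported with a 95% CI. It should come from one repeated-measures model with arm, time and arm-by-time that takes account of the baseline lactate already collected. A two-sample comparison of change from baseline, using a test the section already lists, is an acceptable simpler form. Name the sample that serves as baseline, since section 5.4 lists a preoperative value and one at the start of CPB, while the lactate objective in section 4.4 begins at 10 minutes. Label the paired within-patient tests descriptive and say that they do not support a claim about filtration.

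The cost is a change of wording and slightly more modelling on the same data. The valid comparison may also prove inconclusive. With 20 per arm, a two-sample *t*-test has about 34% power for a difference of 0.5 SD and 69% for 0.8 SD. That limit comes from the sample size, and within-arm tests do not overcome it.

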MUF seeks to achieve more effective hemofiltration by hemoconcentrating the patient and reducing inflammatory mediators [12].

The surgical team at Puerta del Mar University Hospital who are taking part in the research usually use a polysulfone membrane throughout the procedure and perform high-flow continuous ultrafiltration (UF), replacing the filtered volume with Prismasol 2® pharmaceutical solution, which contains the following active substances: calcium chloride, dihydrate; magnesium chloride, hexahydrate; glucose monohydrate, lactic acid solution 90%; sodium chloride; potassium chloride and sodium hydrogen carbonate. This solution is also used for priming the CPB circuit, and it must be taken into account in the research that Prismasol 2® solution contains 3 mEq/L of lactate.

Prismasol 2® solution is used as a solution for hemofiltration in the treatment of renal insufficiency and no contraindications with CPB have been reported, since serum potassium and calcium levels are monitored every 20 minutes. The administration of sodium bicarbonate is also eliminated from priming.

Likewise, CUF during CPB is safe thanks to continuous patient monitoring throughout the procedure.

The flow rates recommended by the manufacturer for the replacement solution in hemofiltration and hemodiafiltration are as follows: Adults and adolescents: 500 - 3000 ml/hour.

The use of hemofiltration in adults during CPB procedures has evolved over the years, with studies showing the advantages of CUF or MUF in CPB procedures, such as increased hematocrit with the consequent reduction in blood transfusions, reduction of inflammatory response, improvement of hemodynamic parameters and better neurological outcomes in patients, as well as a shorter postoperative intubation time in the intensive care unit [13].

There is a disparity in the scientific literature regarding HL during and after CPB, and while Soliman R et al. [14] consider that continuous hemofiltration increases postoperative lactate levels and inotropic drug use, Kiziltepe et al. [15] describe it as a safe procedure in adult patients undergoing cardiac surgery.

Perhaps the results of the Soliman group were conditioned by the use of moderately hypothermic CPB and the use of Ringer's lactate solution at a concentration of 27.8 mEq/L for priming the CPB circuit.

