**4.4.- Specific objectives:**

- To determine plasma lactate levels in patients who undergo CPB at different stages of the process:
  - 10 minutes after starting CPB.
  - Every twenty minutes until the end of the CPB procedure
  - Twenty minutes after stopping CPB.
- To determine lactate levels in the effluent.
- To describe the behavior of variables that may influence intraoperative lactatemia levels.
- To evaluate the effects of using the polysulfone membrane continuously during the intraoperative and postoperative period.
- To describe the epidemiological profile, risk factors and surgical risk, according to the usual scores, of the patients in the study.
- To analyze the complications and side effects deriving from CPB and continuous hemofiltration with volume replacement.
- To identify patients' health status using the NANDA diagnosis classification.
- To assess patients' status of using the Nursing Outcomes Classification (NOC), before and after surgery with CPB.
- To evaluate the efficacy of the Nursing Interventions Classification (NIC), after CPB surgery using the Nursing Outcomes Classification (NOC).

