**5.4.- Description of methods:**

The proposed methods to be used in this study are based on analyses of the following instruments and variables:

- Clinical and analytical instruments.
- Record sheet of variables from the patient's medical record.
- Record sheet of intraoperative variables.
- Graph from the perfusionist and electronic data collection systems.
- Record sheet of postoperative variables.
  - Graph and records from the ICU.
  - Graph and records from the ward.
  - Lactate testing instruments.

The variables to be studied have been selected according to the existing literature regarding the factors associated with the results of the therapy used.

- Dependent variables:
  - Levels of serum lactate in mmol/L (continuous quantitative variable): at the beginning of CPB, after 10 minutes of CPB, every 20 minutes during the procedure and 20 minutes after the end of CPB.
  - Effluent lactate levels in mmol/L (continuous quantitative variable): at the end of the procedure.
  - Intra- or perioperative mortality, yes/no (dichotomous variable).
  - Complications: intubation, seizures, pleural effusion requiring drainage, yes/no (dichotomous variable).
  - Evaluation of the outcome of the intervention by the perfusionist nurse. During CPB. NOC nursing taxonomy in the preoperative period, at the end of each procedure and in the postoperative period. These outcomes consist of indicators that measure the patient's health on a Likert scale (1-5).
- Adjustment or stratification variables:
  - Predicted mortality scale (EuroSCORE[[1]](#footnote-2)).
  - Serum potassium and lactate values, immediately after surgery and with each routine blood analysis in the ICU.
- Preoperative variables:
  - Demographic variables:
    - Age: years (quantitative variable).
    - Sex: male/female (dichotomous variable).
- Biometric variables:
  - Height: centimeters (continuous variable).
  - Weight: kilograms (continuous variable).
    - The above variables will be used to calculate the body mass index (BMI): weight/height2 = kilograms/m2 (continuous variable).
- Biochemical variables:
  - Glucose: mg/dL (continuous variable).
  - Serum lactate: mmol/L (continuous variable).
  - Diagnosis upon admission: according to ICD-9 international classification.
    - Comorbidities: presence/absence in the patient's medical record (dichotomous variables):
      - Arterial hypertension.
      - Hyperlipidemia.
      - Peripheral artery disease.

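### The reference sample for lactate change is defined two ways, one of them on treatment in the hemofiltration arm, and the between-arm test does not use baseline lactate by default

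*Protocol*

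**What the plan says.** Protocol section 5.7 has two bullets that bear on lactate. The first is within patients: "The intrasubject change over time will be analyzed by comparing paired means using a t-test or Wilcoxon signed rank test (non-parametric variables", with the change obtained by "quantifying the change in each measure in relation to the baseline reference measure (first sample". The second compares the control and hemofiltration groups with generic tests (t-test or Mann-Whitney for quantitative variables). It names no lactate measure or time and does not mention the baseline value. A last bullet brings in linear regression, but only if some variable proves to differ between the groups.

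The first lactate sample is described in two places:

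- Section 4.4 (Specific objectives) opens its list of sampling times with "10 minutes after starting CPB". Nothing earlier is listed there.
- Section 5.4 (dependent variables) has serum lactate measured "at the beginning of CPB, after 10 minutes of CPB, every 20 minutes during the procedure and 20 minutes after the end of CPB".

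Section 5.4 also lists lactate among the preoperative biochemical variables ("Serum lactate: mmol/L (continuous variable") without saying whether it can serve as the reference.

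On the start of treatment, section 5.8 says that "a minimum time of 60 minutes is established from start of CPB + CUF and to the end of CPB". The hypothesis in section 4.2 is that continuous ultrafiltration with volume replacement "during CPB in patients undergoing cardiac surgery decreases intraoperative lactatemia".

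**The concern.** Every change value depends on the reference sample, and the protocol gives two. If the 10-minute sample is used, the reference in the hemofiltration arm has already seen 10 minutes of filtration, while the control arm's has not. Any early effect is then subtracted from the quantity meant to show it. The direction is not certain: section 3 notes that the solution used for replacement and for priming "contains 3 mEq/L of lactate", so early exchange could move the value either way, and a sample 10 minutes into bypass also reflects the prime in both arms.

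Separately, the hypothesis is about a difference between arms, whereas the paired tests ask whether a patient's lactate moved during bypass. Section 4.4 implies, and section 3 describes, a lactate course that bypass itself can change, so movement within an arm says nothing about filtration. The between-arm bullet asks the right kind of question but, by default, leaves aside the baseline lactate that section 5.4 already collects. In a trial of about 40 patients that gives up precision.

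**Working it through.** **1. The passages side by side.**

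| Section | First lactate sample | Filtration exposure at that sample, hemofiltration arm |
|---|---|---|
| 4.4 | 10 minutes of bypass | 10 minutes, as 5.8 starts both clocks together |
| 5.4 | beginning of bypass | none to speak of |
| 5.7 | the first one, not identified | depends on which list governs |

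The conflict is established from the text alone. The protocol gives no alpha, power, effect size or SD, so there is no stated figure to reproduce. The numbers below rest on assumptions: two-sided 5% and 20 per arm. Section 5.1 gives eight blocks of five (8 × 5 = 40) but no allocation ratio.

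**2. What an on-treatment reference could cost.** Let d be the true arm difference in change, in SD units of the change, and f the share of it already present in the reference. The observable difference is d(1 − f). Power ≈ Φ(d(1 − f)/√(2/20) − 1.96). With d = 0.886, which gives 80% power at 20 per arm:

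| f (assumed) | d(1 − f)/√(2/20) | Power |
|---|---|---|
| 0 | 2.80 | 80% |
| 0.10 | 2.52 | 71% |
| 0.25 | 2.10 | 56% |
| 0.50 | 1.40 | 29% |

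The documents do not give f. Ten minutes is 10/60 = 17% of the exposure in the shortest eligible bypass and 10/120 = 8% in a two-hour one. Those are shares of exposure time, not of effect.

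**3. Why paired tests cannot decide between arms.** Suppose both arms have the same 0.5 SD rise and there is no treatment effect. With within-patient correlation ρ, the SD of the change is √(2(1 − ρ)). If a paired t-test with n = 20 has power p, the chance that exactly one arm is significant is 2p(1 − p).

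- ρ = 0.5: standardised change 0.5/1.00 = 0.50, p = 0.56, so 2 × 0.56 × 0.44 = 0.49.
- ρ = 0.8: standardised change 0.5/0.632 = 0.79, p = 0.92, so 2 × 0.92 × 0.08 = 0.15.

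Simulation (10,000 runs) agrees: 15% to 50%.

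**4. What baseline adjustment gains.** Take the variance of a follow-up value as 1 and its correlation with baseline as r. An unadjusted comparison of follow-up values has relative variance 1, change scores 2(1 − r), and adjustment for baseline 1 − r².

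| r | Unadjusted follow-up | Change score | Baseline-adjusted |
|---|---|---|---|
| 0.30 | 1.00 | 1.40 | 0.91 |
| 0.50 | 1.00 | 1.00 | 0.75 |
| 0.85 | 1.00 | 0.30 | 0.28 |

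The gain over change scores is clear at low r and small at high r. The gain over unadjusted values runs the other way.

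**5. Multiplicity, only if the arms were tested separately at each sample.** Simulations with no arm difference, 20 per arm, three to eight tests and correlations of 0.5 to 0.85 give roughly a 10% to 26% chance of at least one p < 0.05, against 5% for one test.

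**The case against.** The strongest reply is that section 5.4 is the operational definition of the outcome and 4.4 only a list of objectives. Read so, the first sample is the one at the beginning of bypass and the reference is clean. That is a fair reading, perhaps the more natural one. It makes contamination possible rather than certain, but it does not remove the conflict: 5.7 does not say which list it means.

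Second, a reader might infer that the plan has no between-arm test of lactate. It has one, in the bullet after the paired tests, and section 5.1 frames the trial as a comparison of groups. Nor does 5.7 say that the paired tests are meant to decide the hypothesis, or that they are run arm by arm; the 15% to 50% figure shows only what such a reading would risk.

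Third, a reader might infer that the main hypothesis carries a 10% to 26% false-positive rate. The protocol nowhere says that the arms are tested at every sample. A single time or a summary value fits its text equally well, and the choice may sit in an analysis plan that is not shown.

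What stands is narrower: two incompatible first samples, paired tests that cannot answer 4.2, and a between-arm comparison that uses baseline lactate only if an imbalance happens to appear.

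**Conclusion.** The point holds in this limited form and should be corrected. The contradiction between 4.4 and 5.4 over the sample that 5.7 uses as reference is a matter of text and needs no assumption. That a 10-minute reference would be on treatment in one arm only follows from 5.8. How much effect it would hide cannot be known from the protocol; the loss from 80% to between 71% and 29% power rests on the assumed shares, 20 per arm and two-sided 5%. In particular, the one-sixth share of a 60-minute bypass must not be read as one-sixth of the effect.

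The gain from adjustment depends on a correlation that the protocol does not give: 0.75 against 1.00 for change scores at r = 0.5, but only 0.28 against 0.30 at r = 0.85. The multiplicity range applies only if each sample were tested separately.

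**What to change.** - Reconcile 4.4, 5.4 and 5.7 so that all name the beginning-of-bypass sample, already listed in 5.4, as the baseline. Add the missing line to 4.4, and state in 5.4 that the sample precedes any filtration.
- Keep the paired t and Wilcoxon tests as descriptive only.
- Test the lactatemia hypothesis of 4.2 by one between-arm comparison adjusted for that baseline whether or not the groups look balanced. ANCOVA at one sample is enough; a mixed model over the on-bypass samples is an equally good choice.
- Prespecify that sample as one that every patient reaches within the 60-minute minimum of 5.8. State whether the 20-minute steps run from the start of bypass or from the 10-minute sample, since the last such sample falls at 60 or at 50 minutes accordingly.
- Report the other times as estimates with intervals.

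Cost: wording in three sections and slightly more analysis work. No extra patients are needed, and no sample beyond those in 5.4. If the start-of-bypass sample is not at present drawn before filtration begins, its timing would need a small change.
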